**Figure 1 figure1:**
[figure not shown]
Interactive Guidance Intervention plan for infants born moderately or late preterm with primary and secondary outcome variables recorded during NICU admission and during medical checkups at 2, 6, and 12 months of corrected age. ADBB: Alarm Distress Baby scale; EPDS: Edinburgh Postnatal Depression scale; IES-R: Impact of Event scale–revised; IGI: Interactive Guidance Intervention; NICU: neonatal intensive care; PPQ-M: modified Perinatal Posttraumatic Stress Disorder Questionnaire; SSW: sustained social withdrawal.

### Blinding

#### Participants

The families of the infants born moderately or late preterm, randomly assigned to intervention or control group, will remain blind to which group they belong. Families will receive feedback on their infant’s Alarm Distress Baby Scale score by telephone after the final assessment at the 12-month medical checkup and will be offered further assessment and intervention, if needed.

#### Care Providers

Neonatologists who care for participants during the trial will be aware of whether the infant is in the intervention or control group. The Alarm Distress Baby Scale–trained neonatologists will only perform follow-up for the intervention group, and neonatologists who provide routine pediatric care will only perform follow-up for the control group.

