### Protocol

For this study, in 2017, Bonifacino et al [38] conducted Alarm Distress Baby Scale training in Chile over 4 days which consisted of 30 hours and 12 training modules. The program featured 2 central theoretical modules which covered early interactions and emotional development, emotional deprivation and its consequences, social withdrawal behaviors as an early alarm sign, and the Alarm Distress Baby Scale fundamentals. Subsequently, 10 modules of video training were presented featuring material with infants between 2 and 24 months of age. These infants had attended medical checkups with Alarm Distress Baby Scale–trained and untrained pediatricians. Following the videos, there was an exam to certify the professionals in the use of the Alarm Distress Baby Scale. Fleiss kappa was used to determine if there was agreement between the 11 evaluators regarding diagnosis (normal behavior or sustained social withdrawal). There was a substantial agreement [44] between evaluators (κ=0.794, 95% CI 0.676-0.913; *P*˂.001). Individual kappa values for normal and sustained social withdrawal categories were κ=0.795 and κ=0.794, respectively.

One fundamental element of the training was that the professionals learned not only to detect the sustained social withdrawal behaviors (and to score these behaviors using the Alarm Distress Baby Scale), but also to meaningfully show the parents how—in terms of communication or contact—their infants seek interaction, with the objective of reducing sustained social withdrawal behaviors.

Participants of the study will be recruited during their admission to the neonatal intensive care units by members of the researcher team and enrolled and randomized by a study coordinator to either the intervention or the control group. The infant will be randomized in a 1:1 allocation using SPSS Statistics (version 25.0; IBM Corp), stratified by hospital center (Clinica Alemana de Santiago or Hospital San Jose) in blocks of four. Also, infants will be stratified into two groups, single or twin pregnancy, in order to isolate the intervention effect from that of other covariables (such as mother of twins learning). The Hospital San Jose sample will also be stratified into two groups, whether the infant is included or is not included in the Kangaroo Care program, since only Hospital San Jose currently offers this program that aims to promote mother infant bonding, and which could potentially act as a confounding variable.

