As shown in Figure 1, all infants will receive routine pediatric care during the medical checkups at 2, 6, and 12 months of age, but in addition, infants in the intervention group will also receive the interactive guidance intervention if the Alarm Distress Baby Scale–trained neonatologists detect sustained social withdrawal during these medical checkups. All medical checkups will be video-recorded, and the videos will be assessed by external Alarm Distress Baby Scale–trained evaluators, and at every medical checkup, parents will fill out the Edinburgh Postnatal Depression Scale, the modified Perinatal Posttraumatic Stress Disorder Questionnaire, and the Impact of Event Scale–revised.

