#### Outcome Assessment

The Alarm Distress Baby Scale–trained neonatologists will be blind to the Alarm Distress Baby Scale scores of the external evaluators and to those of the other Alarm Distress Baby Scale–trained neonatologists. Once they record an Alarm Distress Baby Scale score, this data will be collected by a study coordinator, who is blind to the group category.

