### Assessment Instruments

Alarm Distress Baby Scale [9] reliably (Cronbach α=.83) assesses sustained social withdrawal behavior in infants from 2 to 24 months of corrected age during routine physical examination. It consists of 8 items (lack of facial expression, eye contact, general movement, self-stimulation gestures, vocalization, liveliness in response to any stimulation, ability to establish and maintain a relationship, and ability to attract and catch the attention of others) each scored from 0 (normal behavior) to 4 (massively abnormal behavior). A total score of 5 or more indicates sustained social withdrawal behavior. The assessment can be done during routine pediatric checkup by a trained professional, or by assessment of an 8 to 12-minute video of recorded infant behavior during a pediatric checkup.

Edinburgh Postnatal Depression Scale [45] reliably (Cronbach α=.77) assesses the probability of postnatal depression in women. It consists of 10 questions with 4 possible answers for each. Each answer is given a score of 0, 1, 2, or 3 according to the severity of the symptom. The maximum score is 30. A total score of 12 or higher suggests the presence of a postnatal depression disorder. The Edinburgh Postnatal Depression Scale can be administered from 2 months onward, after delivery.

Impact of Event Scale–revised [46] reliably (Cronbach α=.98) assesses symptoms associated with posttraumatic stress disorder. It is composed of 22 items and three subscales: intrusion, avoidance, and hyperactivation. It employs a 5-point Likert scale from 0 (not at all) to 4 (extremely), to assess the intensity of the symptoms. The Impact of Event Scale–revised can be applied from six weeks onward, after the occurrence of a stressful or traumatic event. Scores higher than 24 indicate significant clinical relevance.

Modified Perinatal Posttraumatic Stress Disorder Questionnaire [47] reliably (Cronbach α=.90) assesses posttraumatic stress symptoms in parents including intrusiveness or reexperiencing, avoidance behaviors and hyperarousal, or numbing of responsiveness. It consists of 14 items, which are measured using a 5-point Likert scale from 0 to 4. Parents are instructed to provide responses that reflect their experience during the 4th and 18th month after delivery. The total score can range from 0 to 56. The clinical range for a high-risk parent is set at 19 or higher.

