**Figure 2 figure2:**
[figure not shown]
Summary of the steps of the interactive guidance intervention during medical checkup.

The main objective of this intervention is to reduce sustained social withdrawal behaviors in moderately and late preterm infants by (1) detecting sustained social withdrawal behaviors during medical checkup, (2) becoming attuned with the interaction rhythm of the infant, (3) meaningfully showing parents how their infant seeks to interact by pointing out specific interactive behaviors (every interaction skill displayed by the infant), and ( 4) inviting parents to engage in the interaction.

Infants born preterm have a higher probability of developing sustained social withdrawal, and withdrawn infants show poor performance during interaction [17,49]; therefore, by facilitating parental understanding of the development of their infant, by involving them in the observation of and interaction with their infant [50], and by reinforcing every seeking interactive behavior displayed by the infant during medical checkups, we can reduce sustained social withdrawal in these infants.

In the intervention group, this interactive guidance intervention will be performed if the trained neonatologist detects sustained social withdrawal during the 2, 6, and 12-month medical checkups. The interactive guidance intervention will be performed during the 20 to 30-minute medical checkup and will not require any extra time. The interactive guidance intervention will be supplemented with a written guide for parents called Early Interaction Guidelines. The objective of this written guideline is to enhance the effect of interactive guidance intervention.

In the control group, infants will receive routine pediatric care. At the 2, 6, and 12-month medical checkups (also lasting 20 to 30 minutes), parents will be given a Development Stimulation Guide which has been adapted from Ministry of Health of Chile Guidelines for the Stimulation of Development [51,52].

If any infant in the study (in either the intervention or the control group) shows sustained social withdrawal (a score or 5 or higher on the Alarm Distress Baby Scale) at the 12-month medical checkup, they will be offered additional interventions by the researcher team.

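### The plan does not secure arm-masked rating of the primary outcome, and does not say whose Alarm Distress Baby Scale score is analysed

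*Protocol article*

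**What the plan says.** All references are to the Protocol article.

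- **Who sees the infant.** Under Care Providers, the trained "neonatologists will only perform follow-up for the intervention group, and neonatologists who provide routine pediatric care will only perform follow-up for the control group". The same section says: "Neonatologists who care for participants during the trial will be aware of whether the infant is in the intervention or control group".
- **What is rated, and by whom.** The Protocol section says: "All medical checkups will be video-recorded, and the videos will be assessed by external" evaluators trained in the scale. Assessment Instruments allows rating by a trained professional at the visit or "by assessment of an 8 to 12-minute video of recorded infant behavior during a pediatric checkup".
- **Where the treatment takes place.** In the Intervention section: "The interactive guidance intervention will be performed during the 20 to 30-minute medical checkup and will not require any extra time". It is given in the intervention arm at 2, 6 and 12 months, when the trained neonatologist detects withdrawal (a score of 5 or more).
- **Who is blind to what.** Under Investigator, the principal investigator is also an external evaluator, takes no part in follow-up, and is blind to the trained neonatologists' scores. Under Outcome Assessment, on the trained neonatologists' scores: "Once they record an Alarm Distress Baby Scale score, this data will be collected by a study coordinator, who is blind to the group category".
- **Which score counts.** Primary Outcome Measure names the scale and the three visits, but not the rater.

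**The concern.** The scale is a judgement of behaviours such as eye contact, vocalisation and capacity to relate, cut at 5. The Blinding section goes role by role. It masks the people who handle the data to group, but says so of nobody who makes the judgement. Meanwhile the examiner differs completely by arm, and the treatment lies inside the recorded visit. The guidance is meant to draw infant and parents into interaction, which is what the scale measures. If a rater can tell the arm, or rates footage that includes guidance, a difference between arms could reflect the rating or the moment rather than a change in the infant.

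The open question of which score is analysed adds a second problem. If the trained neonatologist's score were used, it would come from an unmasked treating clinician and would have no control counterpart.

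**Working it through.** The plan gives no figure on this point, so the main check is to set the sections side by side.

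**1. Blinding by role (Blinding section, with Protocol for the external evaluators)**

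| Role | Rates infants? | Stated blind to | Blind to group? |
|---|---|---|---|
| Trained neonatologist | Yes | External evaluators' and other trained neonatologists' scores | No, aware of group |
| Principal investigator as external evaluator | Yes | Trained neonatologists' scores | Not stated |
| Other external evaluators | Yes | Nothing stated | Not stated |
| Data-entry agent | No | Group | Yes |
| Coordinator collecting scores | No | Group | Yes, as stated |
| Data collection assessors | No | Group | Yes |

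No rater is stated to be blind to group.

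**2. Does the rated footage contain the treatment?** The visit lasts 20 to 30 minutes and the rated video 8 to 12 minutes. The clip is therefore between 8/30 = 27% and 12/20 = 60% of the visit. A clip can leave the guidance out, but no rule says that it does.

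**3. Does the neonatologist's score exist in both arms?** Trained neonatologists follow only the intervention arm (Care Providers). The score collected at the visit is theirs (Outcome Assessment). The study's neonatologists are described as the only follow-up neonatologists in Chile trained in the scale (Ethical Considerations). The inference is that controls have no such score. Two things follow:
- it cannot be compared between groups;
- when it reaches the coordinator, its existence reveals the arm.

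In addition, the Protocol section has infants "enrolled and randomized by a study coordinator to either the intervention or the control group". The text does not say whether this is the same coordinator.

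**4. What could be at stake (illustration only).** Inputs from the documents: 55 per group (Sample Size) and prevalence of 11.3% to 22.1% in preterm infants (Introduction). Assumptions not in the documents: no true effect, sensitivity and specificity of 0.90 for control ratings, a shift in the intervention arm, independent infants and no attrition.

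Observed prevalence = Se × p + (1 − Sp) × (1 − p).

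Control: at p = 0.113, 0.90 × 0.113 + 0.10 × 0.887 = 0.190; at p = 0.221, 0.90 × 0.221 + 0.10 × 0.779 = 0.277.

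| True p | Intervention Se, Sp | Intervention observed | Difference | Chance of P<.05 |
|---|---|---|---|---|
| 0.113 | 0.80, 0.90 | 0.0904 + 0.0887 = 0.179 | 0.011 | 5.3% |
| 0.113 | 0.80, 0.95 | 0.0904 + 0.0444 = 0.135 | 0.056 | 12.3% |
| 0.113 | 0.70, 1.00 | 0.0791 + 0 = 0.079 | 0.111 | 40.0% |
| 0.221 | 0.80, 0.90 | 0.1768 + 0.0779 = 0.255 | 0.022 | 5.8% |
| 0.221 | 0.80, 0.95 | 0.1768 + 0.0390 = 0.216 | 0.061 | 11.5% |
| 0.221 | 0.70, 1.00 | 0.1547 + 0 = 0.155 | 0.122 | 34.2% |

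The last column is the normal approximation for a two-sided comparison of two proportions: Φ((d − 1.96·SE0)/SE1) + Φ((−d − 1.96·SE0)/SE1), where d is the difference, SE0 the pooled and SE1 the unpooled standard error at n = 55. With equal accuracy in both arms it is 5%. Swapping the arms gives the same sizes with the opposite sign.

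**The case against.** The strongest reply is that a common measure already exists. External evaluators rate video of every check-up in both arms, and families in both arms are promised a score. A neonatologist's score in one arm does harm only if it is the one analysed. It may be no more than the trigger for guidance or an agreement check. This stands: a reader might infer that ascertainment is shown to differ by arm, but the document supports only that the choice of score is left open.

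Other parts of the reply also stand:

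- Silence on the other external evaluators is not a statement that they know the arm. Only the principal investigator's blinding is described.
- Camera framing is not described, so it is an inference that the clinician can be recognised. Guidance occurs only where withdrawal is detected, and detection is its first listed step, so a rated segment could precede it.
- The absence of control neonatologist scores is inferred, not stated. The two coordinators may be different people.
- Separating clinicians by arm is a reasonable way to keep controls away from trained staff.

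What does not stand is that this is only detail left to a fuller protocol. The article specifies blinding role by role, states group masking for three data-handling roles, and gives the one rater it describes as an external evaluator a different kind of masking. Its claim about the coordinator also sits badly with its own design. The agreement reported from training (κ = 0.794 among 11 evaluators) shows consistency between raters. It does not show that they are unaffected by knowing the arm.

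**Conclusion.** The concern holds in this form: as written, the plan does not secure masked rating of the primary outcome and does not fix which rater's score is analysed. The neonatologist's score cannot serve as a between-group outcome if, as inferred, it exists in one arm only. Its arrival would then unmask the coordinator, whether or not that person also randomises.

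The size of any bias cannot be derived. The illustration runs from about 1 to 12 percentage points, with a false-positive chance from about 5% to 40%, and depends wholly on assumed accuracy shifts.

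Two further readings are tempting but not supported. One is that the bias must favour the intervention. Unmasked rating or in-visit guidance could lower scores in that arm, but clinicians primed to look for withdrawal could raise them if their scores were used. The other is that the 12-month visit is most exposed. Guidance is offered on the same terms at 2, 6 and 12 months, so no visit is singled out.

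**What to change.** 1. Under Primary Outcome Measure, name the external evaluator's video score as the primary outcome in both arms.
2. Under Blinding, state that all external evaluators, including the principal investigator, are masked to group.
3. Rate an 8 to 12-minute segment of the standard examination, cut before any guidance begins. Use the same cutting rule in both arms, code the clips, present them in random order, and hide the clinician's identity where feasible.
4. Keep the neonatologist's score for its role within the intervention and out of the between-group analysis.
5. Correct or qualify the statement that the coordinator collecting those scores is blind to group.

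The cost is editing and coding the videos and some re-scoring by the existing evaluators. Enrolment was complete by May 2020, so visits already filmed can only be edited, and some may lack 8 minutes before guidance; count and report these. Masking will be imperfect. Editing cannot remove the difference in how trained and untrained clinicians elicit behaviour, which should be stated under Study Limitations.

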### Statistical Analysis

Two-tailed paired *t* tests will be used to compare covariates and dependent variables from the infant groups. A one-way analysis of covariance will be used to determine the effects of covariates (sociodemographic and neonatal intensive care unit hospitalization variables, postpartum depression, and posttraumatic stress) on the comparisons between groups (control and intervention) and between times (2, 6, and 12 months of corrected age medical checkups) regarding the dependent variable (sustained social withdrawal). Other statistical techniques such as matching, odds ratios, and logistic regression will also be used.

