## Discussion

### Summary

This project is a logical continuation of the work in Bonifacino et al [38] and aims to contribute to the early detection of alarm signs in emotional development and early intervention to help infants born moderately or late preterm. Neonatologists have a central role to play in this regard, and based on the findings of both Bonifacino et al [38] and Facchini et al [40], we hypothesize that implementing interactive guidance intervention will reduce sustained social withdrawal in infants born moderately or late preterm compared to those who receive routine care. Also, we hypothesize that this interactive guidance intervention will be easily implemented and accepted by patients and their families.

This is the first randomized controlled trial that will be performed with infants born moderately or late preterm at follow-up pediatric checkups. The implementation of an interactive guidance intervention will allow Alarm Distress Baby Scale–trained professionals who use this interactive guidance intervention as a model to intervene for infants at risk.

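### Each neonatologist follows only one arm and conducts the checkup from which withdrawal is scored, but the stated analysis has no neonatologist term and the hypothesis credits the guidance alone

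*Protocol article*

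**What the plan says.** **Who sees whom.** Methods, Blinding, Care Providers states that the scale-"trained neonatologists will only perform follow-up for the intervention group", while "neonatologists who provide routine pediatric care will only perform follow-up for the control group". Both sets of clinicians know the allocation: "Neonatologists who care for participants during the trial will be aware of whether the infant is in the intervention or control group".

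**Where the outcome comes from.** Methods, Protocol: "All medical checkups will be video-recorded, and the videos will be assessed by external" evaluators trained in the scale. Assessment Instruments allows scoring by a trained professional during the checkup or "by assessment of an 8 to 12-minute video of recorded infant behavior during a pediatric checkup". Either way, the behaviour scored is what the infant shows during a visit run by the arm-specific neonatologist.

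**How it is analysed.** Statistical Analysis names t tests and then: "A one-way analysis of covariance will be used to determine the effects of covariates". The covariates listed are sociodemographic and neonatal-unit variables, postpartum depression and posttraumatic stress. Matching, odds ratios and logistic regression are added. No neonatologist effect is named. Sample Size allows for attrition and a margin on the effect size, with no mention of shared clinicians.

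**What the difference is credited to.** Discussion, Summary: "we hypothesize that implementing interactive guidance intervention will reduce sustained social withdrawal in infants born moderately or late preterm". The Abstract's Objective and the aim that closes the Introduction are framed the same way. Study Limitations discusses information passing between parents and the two hospitals' pain protocols, but not the separation of clinicians.

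**The concern.** Two separate problems follow.

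**Precision.** Infants examined by the same neonatologist share that person's manner of conducting a visit. If this makes their scores more alike, 55 infants per arm carry less information than 55 independent ones. An analysis without a neonatologist term then gives intervals that are too narrow and a type I error above 5%.

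**Attribution.** Randomisation balances the infants. It does not balance the examiners, who are assigned by arm. Any systematic difference between the two sets of neonatologists falls wholly on the arm comparison. Guidance goes only to intervention infants in whom withdrawal is detected, whereas every intervention infant is examined by a trained neonatologist. An arm difference could therefore arise partly in infants who received no guidance. Video scoring by external evaluators does not remove this, because the filmed behaviour took place with the arm-specific examiner.

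At stake are the width of the reported interval and what a positive result would allow the investigators to say.

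**Working it through.** **1. The plan's own figure.** Inputs from Sample Size: 57% against 13%, α = 0.05 (taken as two-sided), power 0.80.

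n = [1.96·√(2·0.35·0.65) + 0.842·√(0.57·0.43 + 0.13·0.87)]² / 0.44² = (1.322 + 0.504)² / 0.1936 ≈ 17.2, so 18 per group.

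With continuity correction: (17.2/4)·[1 + √(1 + 4/(17.2·0.44))]² ≈ 21.5, so 22. Fisher's exact test also needs 22 (power 0.826; 0.850 at 23). The stated 23 per group is thus reproduced to within one infant, with no allowance for clustering. The increase to 55 may absorb some clustering, but it does not change how the standard error is calculated.

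**2. Effect of shared neonatologists.** Input from the article: 55 infants per arm. Assumptions, because the article does not give them: k neonatologists per arm (2 to 8), an even split, one neonatologist per infant, and a within-neonatologist correlation ρ of 0.01 to 0.10. The 11 evaluators under Protocol are those in the training exam, not the treating neonatologists, so they do not fix k.

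- Infants per neonatologist: m = 55/k
- Design effect: DE = 1 + (m − 1)·ρ
- True standard error = planned standard error × √DE
- True type I error of a nominal 5% test = 2·[1 − Φ(1.96/√DE)]

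Example, k = 3 and ρ = 0.05: m = 18.3, DE = 1 + 17.3·0.05 = 1.87, √DE = 1.37, effective sample 55/1.87 ≈ 29.5 per arm, error = 2·[1 − Φ(1.43)] ≈ 15%.

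| k per arm | ρ = 0.01: SE factor, error | ρ = 0.05: SE factor, error | ρ = 0.10: SE factor, error |
|---|---|---|---|
| 2 | 1.12, 8.1% | 1.52, 19.9% | 1.91, 30.5% |
| 3 | 1.08, 7.0% | 1.37, 15.1% | 1.65, 23.6% |
| 5 | 1.05, 6.2% | 1.22, 11.0% | 1.41, 16.6% |
| 8 | 1.03, 5.7% | 1.14, 8.5% | 1.26, 12.0% |

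Simulation with 20,000 trials per setting agrees for ρ = 0.01, 0.05 and 0.10: 7.7%, 20.5%, 31.3% for k = 2; 7.0%, 15.3%, 23.9% for k = 3; 6.2%, 11.2%, 16.7% for k = 5.

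**3. Power once clustering is allowed for.** For 57% against 13% with 55 per arm, power is 99.9% if clustering is ignored. With ρ = 0.05 and 2(k − 1) degrees of freedom it is 49% (k = 2), 84% (k = 3), 97% (k = 5) and 99% (k = 8).

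**4. How many infants would receive guidance.** The Introduction cites a prevalence of 11.3% to 22.1% in preterm infants. If that applied here, 55 × 0.113 ≈ 6 to 55 × 0.221 ≈ 12 intervention infants would show withdrawal at a given visit. The remaining 43 to 49 would meet a trained examiner without guidance.

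**5. Separability.** Neonatologist is nested in arm with no overlap. A random neonatologist effect can estimate variation among clinicians within an arm. It cannot separate the average difference between the two sets of clinicians from the effect of guidance.

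**The case against.** **The design is deliberate.** Trained clinicians cannot unlearn the method, so separating them by arm is a sensible guard against contamination. This stands, and the design need not change.

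**This is a matter for the analysis plan.** A short statistical paragraph in a journal article may leave a random effect and degrees of freedom to a document not shown here. That is fair, and the absent model detail alone would not be a finding. But the article does fix the clinician separation, the named tests, the covariates and the attribution. A random effect added elsewhere would not correct the attribution.

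**The size is assumed.** This stands in full. A reader might infer that the standard errors are known to be wrong by some definite amount. The documents do not support that: with 8 neonatologists per arm and a correlation of 0.01 the error is about 6%, and with no correlation there is no inflation.

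**Examiner skill is inferred.** A reader might take "becoming attuned with the interaction rhythm of the infant" as proof that trained neonatologists behave differently at every filmed visit. Under Intervention it is a step of the guidance itself, following detection. A separate examiner effect is plausible, but it is not documented.

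**The article already names trained clinicians.** A reader might infer that it flatly overclaims. It states a hypothesis, its Abstract conclusion is conditional on success, and the Abstract, Introduction and Study Design partly tie the intervention to trained neonatologists. The wording needed is therefore a tightening.

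**Conclusion.** The point holds as an inexpensive improvement. Clinicians are fully separated by arm, they conduct the checkup that is scored, no stated analysis accounts for them, and the aim and hypothesis name the guidance as the cause. If the analysis is run as written, the standard errors are too small whenever the within-neonatologist correlation is above zero. Under the assumptions set out above, the true type I error lies between about 6% and 31%. These figures illustrate the possible size; they are not estimates for this trial.

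The limit on attribution does not depend on those assumptions. The trial can compare two kinds of follow-up, but it cannot isolate the guidance from the clinicians who deliver it.

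A reader might think the 2-month score offers a clean check for an examiner effect, or a baseline to adjust for. The documents do not support this. Guidance may be given within the filmed 2-month visit, and nothing says that the scored segment ends before it starts. The score is also taken after randomisation and may already be shifted by the arm-specific examiner.

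**What to change.** 1. **Wording.** State the comparison and the conclusion as follow-up by a scale-trained neonatologist, with guidance on detection and the written guide, versus follow-up by a routine-care neonatologist. Add the nesting of neonatologist in arm to Study Limitations.

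2. **Data and analysis.** Record the examining neonatologist at every visit, and for visits already completed recover the identity from recordings or clinic records where possible. Before analysis, pre-specify a sensitivity analysis with a neonatologist effect nested in arm and small-sample degrees of freedom. If that model cannot be estimated, report the confidence interval inflated by √DE over a stated range of correlations, such as 0.01 to 0.10, using the actual numbers of infants per neonatologist.

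Do not use the 2-month score as an examiner check or as an adjustment covariate for this purpose.

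**Cost.** An identifier, one additional analysis and some rewording; the design and sample size stay as they are. The interval widens: with 3 neonatologists per arm and a correlation of 0.05, a clustered analysis on 4 degrees of freedom gives an interval about 2.776 × 1.37 / 1.98 ≈ 1.9 times as wide as the planned one. The claim also narrows. The neonatologist effect repairs the error bars, not the confounding, so the second change does not replace the first.
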